## 4.5. Withdrawal of Consent or Participant

Participants may be withdrawn from the study if:

- They experience a serious adverse event that:
  - is attributable to a study intervention or procedure; or
  - means they can no longer participate in the study; or
- They withdraw consent to take part.
- We will not be replacing participants that are withdrawn from the study.

The team clinical psychologist will follow-up with subjects withdrawn due to experiencing a serious adverse event that was attributable to the study intervention or procedure. These participants will be contacted via email within 72 hours of withdrawing from the trial with a list of crisis contact numbers for support. In this email, participants will also be asked to respond to the email (by clicking ‘reply’) if they would like to receive a phone call from the team clinical psychologist during business hours (9:00 to 17:00 AEST). If they say yes, they will be contacted within the following 72 hours.

Participants can self-withdraw at any time by submitting to the study team the UNSW standard withdrawal form appended to the Participant Information Statement and Consent Form. No mechanisms for automated withdrawal (e.g. via the study app) will be provided. To ensure that data belonging to a participant who withdraws can be uniquely identified, their mobile number and email address will be solicited on the withdrawal of participation form. Excluding self-withdrawals, the decision to withdraw a participant will be made by the Principal Investigator.

Handling of participant data after withdrawal will depend on when a participant decided to withdraw from the study. Participants will have their data removed from the study if they:

- Withdraw or are withdrawn prior to completion of the baseline assessment. Reflecting the intention-to-treat principles informing the planned analyses of the trial, data from participants who withdraw after this point will not be discarded.

For those who install the app, access the app once, and complete baseline, subsequent non-response (rather than active withdrawal) will not be treated as withdrawal but handled as missing data unless the specifically request to have their data withdrawn.

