Non-identifiable data about withdrawals enabling aggregate reporting (e.g. counts by intervention assignment) will be retained in a Withdrawals Log. In addition, any participant withdrawal linked to an adverse event will be recorded to enable reporting of safety-related statistics. Participants who withdraw from the study will not be replaced and will not be followed up except per adverse event follow-up, if applicable.

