# Statistical Analysis

Mixed models repeated measures analyses, with maximum likelihood estimation and an appropriate covariance structure, will be used to evaluate the efficacy of the Lifebuoy app relative to the control condition. The primary outcome is severity of suicidal ideation as assessed by the Suicidal Ideation Attributes Scale [SIDAS] over time (pre- test to post-test; pre-test to follow-up). The mixed models approach incorporates all available data, including participants with missing follow-up data points, under the missing- at-random assumption. Analyses will therefore accord with the intention-to-treat principle. This same approach will be used to examine reductions in secondary outcomes (depression (PHQ-9) anxiety (GAD-7) psychological distress (DQ-5) and wellbeing (SWEMWBS)) and tertiary outcomes (rumination (RTQ-10) insomnia (ISI) general mental wellbeing (SWEMWBS) help-seeking (GHSQ, CSRI)) over time.

Potential mechanisms of the symptom reduction will be measured by the changes in the levels of distress tolerance (DTS), loneliness (TILS) or suicide cognition (SGS). Negative life events (NLESS), grit (SGS) and questions about expectation of treatment success are included in the surveys as potential moderators. Participants’ current medications/interventions will be controlled for data analysis.

Descriptive statistics will be used to evaluate app engagement for participants in both conditions. Adherence will be indicated by the number of modules completed by participants. Participant module access and module completion will be automatically collected via the app. The mixed model approach will be used to determine whether adherence moderates the change in SIDAS scores over time in the intervention condition.

Acceptability of the LifeBuoy app will be examined through semi-structured interviews with a subset of participants and questionnaires in the survey. The interview data will be analysed using thematic analysis [40]. An inductive approach, independent of a theoretical confirmative method will be used to identify and group themes. The researchers will then refine the themes and determine the final coding framework. Discrepancies will be resolved by a third researcher to ensure reliability of the process.

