# Sample size

Based on a systematic review and meta-analysis [8], an effect size of 0.30 (Cohen’s d) will be expected between the intervention condition and the control condition at post-test in terms of suicidal ideation as measured by the SIDAS (Appendix C). Based on an attrition rate of 30% and a 0.50 correlation between pre- and post-test SIDAS scores, a sample size of n = 189 in each condition (total N = 378) will detect this expected effect size with power = 0.80 and alpha = 0.05. The planned sample size of n = 189 for the intervention condition will also allow statistical power of at least 0.80 to detect small-to-medium size effects in moderation analyses.

For the qualitative interviews we aim to recruit 10% of participants from the Intervention condition. This will result in a subsample of qualitative interviews of approximately n=20 persons based on a recruitment target of n=189 in each condition. In prior qualitative studies that have examined users’ experience with an app for managing psychological and physical health conditions, the sample sizes ranged from between 15 and 25 participants [41 – 43] which indicates our sample size is acceptable and justifiable.

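### Section 4.5 does not separate stopping the app from leaving outcome assessment, so a consenting participant withdrawn for an attributable serious adverse event would have no later T1/T2 SIDAS

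*Protocol*

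**What the plan says.** Section 4.5 lists the grounds on which a participant may be withdrawn from the study. One begins "They experience a serious adverse event that" and continues with two alternatives: the event is attributable to a study intervention or procedure, or it means the person can no longer take part. Withdrawal of consent is a separate ground. On who decides: "Excluding self-withdrawals, the decision to withdraw a participant will be made by the Principal Investigator".

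After withdrawal, section 4.5 says: "Participants who withdraw from the study will not be replaced and will not be followed up except per adverse event follow-up, if applicable". For attributable serious adverse events it describes a support email and an optional call from the team psychologist. Neither collects an outcome measure.

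Three provisions limit the consequences:
- Data from anyone withdrawn after baseline are retained, with intention-to-treat given as the reason.
- Withdrawals linked to an adverse event are recorded for safety reporting.
- A participant who has installed and opened the app, completed baseline and then simply stops responding is treated as having missing data, not as withdrawn.

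Section 7 fits a mixed model to all available data, "including participants with missing follow-up data points, under the missing- at-random assumption", and concludes from this that the analysis follows intention-to-treat.

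**The concern.** The protocol provides no status for a participant who stops using the app but remains under assessment. A person who still consents, but whom the investigator withdraws after an attributable serious adverse event, leaves both at once. In a trial whose primary outcome is suicidal ideation, a serious event attributable to participation may well be related to the score that is then not collected.

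Two things are at stake. First, the T1 comparison of SIDAS relies on the model predicting missing scores from observed ones. If the event occurs before T1, the only scheduled SIDAS value is the baseline one, which precedes the event and carries no information about it. Second, two safety measures in the DSMB charter (Appendix E, Safety Analyses) draw on the same surveys: the percentage scoring above 20 on the SIDAS, and attempts in the past 30 days reported at post-intervention or follow-up. Later survey answers from these participants would be absent.

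This is a rule about data collection. A sensitivity analysis may be planned elsewhere, but no analysis recovers a survey that was never sent.

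**Working it through.** **1. Does the no-follow-up sentence cover investigator withdrawals?** It speaks of participants who withdraw, which could mean self-withdrawal only. Two features of section 4.5 point the other way. It describes those withdrawn for a serious adverse event as withdrawing from the trial, and the exception for adverse event follow-up makes most sense if such participants are included. Inclusion is the natural reading but not an explicit one.

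**2. What does the model hold for them?** The schedule in section 6.5 has SIDAS at baseline, post-intervention (T1) and final follow-up (T2). The week-3 SIDAS safety check in section 12.1 is not in that schedule. An event before T1 therefore leaves baseline only. An event after T1 leaves baseline and T1, so the post-intervention comparison in H1 is intact and only T2 is lost.

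**3. Is the sample size affected?** Inputs from section 8: "an effect size of 0.30" (Cohen's d); "Based on an attrition rate of 30% and a 0.50 correlation between pre- and post-test SIDAS scores"; "with power = 0.80 and alpha = 0.05". Sidedness is not stated; two-sided is assumed.
- Baseline-adjusted SD = √(1 − 0.50²) = √0.75 = 0.866.
- Completers per arm for d = 0.30: 131 by the normal approximation, 132 by the noncentral t.
- Inflated for attrition: 132 / (1 − 0.30) = 188.6, so 189 per arm and 378 in total. The stated figure reproduces.
- Completers expected: 189 × 0.70 = 132.3 per arm, power 0.804.

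A few withdrawals for serious adverse events fit within the 30% attrition allowance. The question is bias, not power.

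**4. How large could the bias be?** The protocol gives no serious adverse event rate and no SIDAS standard deviation, so these are assumptions:
- SD = 10 points, so the targeted effect is 0.30 × 10 = 3 points.
- A proportion q of the intervention arm is withdrawn before T1, and none in control.
- Their true T1 scores lie 10 to 20 points above the model's prediction. The scale allows this (eligibility below 21 on a 0–50 scale), but the protocol does not supply it.

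Bias in favour of the app = q × excess.

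| q | About how many of 189 | Bias (points) | Share of 3 points |
| --- | --- | --- | --- |
| 1% | 1.9 | 0.1–0.2 | 3–7% |
| 3% | 5.7 | 0.3–0.6 | 10–20% |
| 5% | 9.5 | 0.5–1.0 | 17–33% |

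The same calculation without an assumed SD uses k withdrawn participants whose scores are D standard deviations worse than predicted: bias = (k/189) × D.
- k = 2, D = 0.5: 0.005 SD, or 2% of 0.30.
- k = 4, D = 1: 0.021 SD, 7%.
- k = 10, D = 1: 0.053 SD, 18%.
- k = 10, D = 2: 0.106 SD, 35%.

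**5. Withdrawals in both arms.** The net bias is the intervention-arm product minus the control-arm product. With equal proportions and equal excess it is zero.

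**The case against.** Withdrawal is discretionary. Nothing obliges the investigator to withdraw anyone after a serious adverse event, and what adverse event follow-up includes is not defined. This stands, and it is why the point concerns what the wording permits and not what must happen.

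The affected group is narrow. A SIDAS score above 20 is an expected adverse event under section 10.1, and at the week-3 check section 12.1 answers it with psychologist contact and referral, not withdrawal. Serious events are the short list in section 10.3, and the charter places the trial in its lowest risk category. Where an event truly prevents participation, as with death, the missing survey is unavoidable. This also stands, and it makes the low end of the range plausible.

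The triggering event is not lost. Section 4.5 records withdrawals linked to adverse events and keeps counts by arm. The charter analyses all serious adverse events and accepts ad hoc reports of attempts. A reader might infer that harms disappear from the safety data. They do not: what goes missing is the later survey answers.

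A reader might also infer that the rule contradicts intention-to-treat and missing at random. It does not. Data collected before withdrawal are kept, and missing at random is stated as an assumption, which this rule makes harder to defend.

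Finally, section 10.3 defines serious adverse events as unrelated to the trial intervention. Read literally, this leaves no events in the intervention-attributable category of section 4.5. That is a conflict between the two sections and does not answer the concern.

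**Conclusion.** The point holds in a limited form. A consenting participant withdrawn at the investigator's discretion for an attributable serious adverse event would, on the natural reading of section 4.5, have no further T1 or T2 assessment. For events before T1 this ties a missing primary outcome to a harm arising after randomisation, with only baseline SIDAS available to predict it. It weakens the basis claimed in section 7 and thins the survey-based safety measures.

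The size cannot be established from the protocol. It is near zero if such withdrawals are very few or balanced between arms. The range of 0.1 to 1.0 SIDAS points, or 3% to 33% of the targeted effect, rests wholly on the assumed SD, excess and withdrawal proportions, and on all withdrawals falling in the intervention arm. That last assumption is possible, since section 10.1 names distress from therapeutic activities on the app as a known harm and the control app is non-therapeutic, but nothing in the protocol establishes it. The upper figure should not be read as an expected bias. The planned 189 per arm is unaffected.

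**What to change.** In section 4.5, define two separate statuses: (i) stopping the assigned app, and (ii) withdrawing from outcome assessment. Limit the no-follow-up sentence to participants who withdraw consent to assessment. Those who still consent would continue to be offered the T1 and T2 surveys, unless the study clinician considers survey contact unsuitable. That exception should expressly cover events attributable to a study procedure, such as the questionnaires themselves, which section 10.1 names as a possible source of distress. State what adverse event follow-up includes. None of this alters when app use is stopped.

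Reconcile section 4.5, which refers to serious adverse events attributable to the intervention, with section 10.3, which defines them as unrelated to it.

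The cost is protocol and consent wording. Section 3.1 already has survey links sent automatically, and the sample size does not change. The downside is a few more survey invitations to people who have had a serious event, which the clinician exception is there to limit.

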## 5.2. LifeBuoy-C (control condition)

For our control condition we created a sham app, LifeBuoy-C, which is designed to match LifeBuoy on expectancy and time on task to control for digital placebo effects. Similar to the intervention app, the control app contains seven brief non-therapeutic education-based modules. The topics are peripherally related to mental health and wellbeing, including confidence, performance stress, the importance of having goals, and the value of being present. Each module takes two to three minutes to read through. The control does not contain the toolbox but includes the help button for safety management. Participants in the control group will be granted access to the intervention app after they complete the three-month follow-up assessment.

At the completion of the final assessment, participants in the control condition will receive an email letting them know they received the non-therapeutic app (Appendix G). The email explains what being in the control condition meant, and why it is important to have a control condition when trying to establish the efficacy of an intervention. Within this email, they will be offered the opportunity to download, and have access to, the Lifebuoy therapeutic app for 6 weeks. The link to the app download will be embedded in the email. This will be the only communication regarding the app download, no additional reminders will be sent. Participants will be able to download the app at any point during that 6 week period. If they attempt to download it after the 6 weeks they will receive the following email: “Oops, looks like the link to the LifeBuoy has expired as it’s been longer than 6 weeks. We’re really sorry about that. If you’re not feeling great, please speak to your GP or call a crisis help line, such as LifeLine [name] or the Suicide Call Back Service [name]”.

# Outcomes and Schedule of Surveys

## 6.1. Primary outcome measure

**Suicidal Ideation Attributes Scale**

The primary outcome measure is the severity of suicidal thoughts assessed by the Suicidal Ideation Attributes Scale (SIDAS; van Spijker, Batterham [23]). It consists of five questions pertaining to frequency of suicidal thoughts in the past month, controllability of suicidal thoughts, closeness to suicide attempt, level of distress associated with the thoughts, and impact on daily functioning. Each item is assessed on a 11-point scale (0-10). Item two (controllability) is reverse scored. Total scale scores on the SIDAS range from 0 to 50, with higher scores indicating more severe suicidal thoughts.

## 6.2. Secondary outcome measures

**Suicide Behaviours**

Participants’ previous suicide attempts and self-injury are assessed by eight questions developed for a previous suicide prevention trial [23]. Participants are invited to indicate whether they have attempted suicide in their lifetime and in the past 30 days on a three-point Likert scale, ranging from ‘No, never (0)’, ‘Yes, once (1)’, to ‘Yes, more than once (2)’. They are also asked to report the number of suicide attempts over their lifetime, and the number of months that they have been thinking about suicide. Apart from that, participants are asked to indicate whether they have intentional self-injury in their lifetime on the aforementioned three-point Likert scale. If yes, they are asked to provide the number of times of their intentional self-injury and rate the severity of the worst injury in the past month on a three-point Likert scale, ranging from ‘No care was needed (1)’, ‘Some care was needed (2)’, to ‘Required medical care (3)’.

**Depression symptoms**

Patient Health Questionnaire-9 (PHQ-9; Kroenke, Spitzer [24]) is a nine-item self-report questionnaire measuring the severity of depression. The scale assesses the frequency of occurrence of depression symptom in the previous two weeks, with items rated on a four-point scale ranging from ‘Not at all (0)’ to ‘Nearly every day (3)’. Total scores on the PHQ-9 depression scale can range from 0 to 27, with higher scores reflecting more severe depression.

**Generalised Anxiety Symptoms**

The Generalised Anxiety Disorder-7 (GAD-7; Spitzer, Kroenke [25]) is a seven-item self-report measure designed to assess the severity of generalised anxiety symptoms over the previous two-week period. Items are responded to a four-point scale, ranging from ‘Not at all sure (0)’ to ‘Nearly every day (3)’. Total scores on the GAD-7 can range from 0 to 21. Higher scores indicate higher levels of GAD symptoms.

**Psychological Distress**

The Distress Questionnaire-5 (DQ-5; Batterham, Sunderland [26]) is a five-item brief screening tool for identifying general psychological distress. Participants are asked to endorse the frequency of each item in the past 30 days on a five-point scale ranging from ‘Never (1)’ to ‘Always (5)’. Total scores range from 5 to 25, with higher scores indicating greater psychological distress.

Short Warwick-Edinburgh Mental Wellbeing Scale

**Wellbeing**

The Short Warwick–Edinburgh Mental Well-Being Scale (SWEMWBS; Fat, Scholes [27,28] is a shortened seven-item version of the 14-item Warwick–Edinburgh Mental Well-Being Scale (WEMWBS) [28], which was developed to assess mental well-being in the general population. It assesses mental wellbeing by asking participants’ feeling and experience over the previous two weeks. Responses range from ‘None of the time (1)’ to ‘All of the time (5)’ and raw item-scores are summed and converted to a metric total score using the SWEMWBS conversion table [35]. Total scores can range from 7 to 35, with higher scores indicating higher levels of mental well-being.

## 6.3. Tertiary outcome measures

**Insomnia Symptoms**

The Insomnia Severity Index (ISI; Morin, Belleville [29]) is a psychometrically sound, seven-item self-report measure assessing the perceived severity of insomnia symptoms, the degree of satisfaction with sleep, interference with daytime functioning, noticeability of impairment, and concern caused by the sleep problems in the previous two weeks. Responses are reported on a five-point scale yielding total scores of 0 to 28. Higher scores indicate greater insomnia severity.

**Repetitive Thinking**

The Repetitive Thinking Questionnaire (RTQ-10; McEvoy, Mahoney [30]) is a transdiagnostic measure of engagement in repetitive negative thinking following distressing situations. The RTQ was developed to capture the underlying construct of recurrent negative thinking underlying mental health disorders such as depression and anxiety. Participants are requested to respond to the RTQ-10 on a five-point Likert scale ‘Not true at all (1)’ to ‘Very true (5)’. Total scores fall between 10 and 50, higher scores indicating greater rumination.

**Suicide Cognitions**

The shortened version of Suicide Cognitions Scale (SCS; Bryan, Kanzler [31]) is a self-report instrument consisting of nine items that are designed to measure suicide-specific cognition. The items contain statements consistent with the suicidal schemas of unbearability (e.g., ‘I can’t cope with my problems any longer’), unlovability (e.g., ‘I am completely unworthy of love’) and unsolvability (‘Nothing can help me solve my problems’). Items on the SCS are rated on a 5-point Likert scale from ‘Strongly disagree (1)’ to ‘Strongly agree (5)’. The instrument is scored by summing ratings across items, resulting in scores ranging from 9 to 45.

**Distress Tolerance**

The Distress Tolerance Scale (DTS; Simons and Gaher [32]) is a 15-item self-report measure designed to assess respondents’ perceived capacity to experience and endure negative emotional states. The DTS encompasses four subscales, including tolerance, appraisal, absorption, and regulation. Items are rated on a five-point Likert scale from ‘Strongly disagree (1)’ to ‘Strongly agree (5)’. Higher mean scores indicate a greater tendency to withstand emotional distress.

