## 1.3. Tertiary Aims

To examine the engagement with the smartphone application in each condition, assessed as uptake (no. downloads), adherence (no. modules completed) and acceptability among intervention condition participants.

To examine whether there is a dose-response relationship between engagement with the application and the primary outcome (suicidal ideation).

To assess whether the LifeBuoy app significantly reduces insomnia, rumination, suicide cognitions, distress tolerance, and help-seeking intentions and behaviours at post-intervention and three-month follow-up relative to control condition.

To examine whether loneliness, demographics, perseverance, negative events (i.e., such as COVID-19), and expectation of treatment success mediate the relationship between allocated condition and the primary outcome (suicidal ideation).

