**Help-Seeking**

The General Help-Seeking Questionnaire (GHSQ; Wilson, Deane [34]) is used in the current trial to assess participants’ intentions to seek help for suicidal thoughts from a variety of sources. Respondents are invited to rate, on a six-point scale from ‘Not applicable (0)’, ‘Extremely unlikely (1)’ to ‘Extremely likely (5)’, the likelihood of seeking help from three professional sources (school or university counsellor, mental health professional, Doctor/GP), four informal sources (boyfriend/girlfriend, friends, parents, other relative/family members), three telephone/online sources (phone helpline, internet website, mobile app) or no one. An optional item, ‘I would seek help from another source not listed above,’ is also provided. Higher scores represent stronger intentions to seek help.

The adapted version of Client Service Receipt Inventory (CSRI; Beecham and Knapp [35]) is designed to collect information about use of healthcare and social care services over a retrospective period of the past six months. Respondents are asked to indicate whether they have used any services in the past six months due to mental health problems, including suicidal thoughts on a binary scale (‘Yes’/’No’). Services include: hospital services, mental health helpline, crisis support team, police/ambulance, contact with a range of mental health professionals (e.g., social worker, counsellor), self-help group, and other medically qualified doctor.

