**Suicidal Ideation Attributes Scale (SIDAS)**

**Now we’re going to ask you some questions are about your suicidal thoughts, and the severity of them.**

**Please think about the past month when answering the following questions.**

##

| In the past month, how often have you had thoughts about suicide? | | | | | | | | | | |
| --- | --- | --- | --- | --- | --- | --- | --- | --- | --- | --- |
| 0  Never | 1 | 2 | 3 | 4 | 5 | 6 | 7 | 8 | 9 | 10  Always |
| In the past month, how much control have you had over these thoughts? | | | | | | | | | | |
| 0  No control | 1 | 2 | 3 | 4 | 5 | 6 | 7 | 8 | 9 | 10  Full control |
| In the past month, how close have you come to making a suicide attempt? | | | | | | | | | | |
| 0  Not close | 1 | 2 | 3 | 4 | 5 | 6 | 7 | 8 | 9 | 10  Made an attempt |
| In the past month, to what extent have you felt tormented by thoughts about suicide? | | | | | | | | | | |
| 0  Not at all | 1 | 2 | 3 | 4 | 5 | 6 | 7 | 8 | 9 | 10  Extremely |
| In the past month, how much have thoughts about suicide interfered with your ability to carry out daily activities, such as work, household tasks or social activities? | | | | | | | | | | |
| 0  Not at all | 1 | 2 | 3 | 4 | 5 | 6 | 7 | 8 | 9 | 10  Extremely |

**We’d just like to ask you a few more questions about prior self-harm behaviour. Just to remind you, these questions are completely voluntary.**

| **What the user will see** | | **Drop down response options available** |
| --- | --- | --- |
| Have you ever attempted suicide? | --- select ---- | No, never Yes, once  Yes, more than once |
| If more than once, how many times? | --- select ---- | 2  3  4  5  6+ |
| How many months have you been thinking about suicide? | --- select ---- | 1 or less  2  3 to 6  >6 to 12  >12 to 24  >24 to 36  >36 |
| How often, on average, do you think about suicide? | --- select ---- | Daily Weekly Monthly  Less than monthly |
| Have you attempted suicide in the past 30 days? | --- select ---- | No, never Yes, once  Yes, more than once |
| Have you ever injured yourself on purpose (i.e., intentional, self-inflicted damage to the surface of the body without suicidal intent) | --- select ---- | No, never  Yes, once  Yes, more than once |
| In the past month, how often have you injured yourself on purpose? | - If ‘Yes, more than once’ then select - | 2-5 times (low)  6-9 times (moderate)  10-20 times (high)  20+ times (severe) |

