**Distress Tolerance Scale (DTS)**

**Think of times that you feel distressed or upset. Select one answer per line that best describes your beliefs about feeling distressed or upset.**

| Feeling distressed or upset is unbearable to me | | | | |
| --- | --- | --- | --- | --- |
| Strongly disagree | Mildly disagree | Agree and disagree equally | Mildly agree | Strongly agree |
| When I feel distressed or upset, all I can think about is how bad I feel | | | | |
| Strongly disagree | Mildly disagree | Agree and disagree equally | Mildly agree | Strongly agree |
| I can’t handle feeling distressed or upset. | | | | |
| Strongly disagree | Mildly disagree | Agree and disagree equally | Mildly agree | Strongly agree |
| My feelings of distress are so intense that they completely take over. | | | | |
| Strongly disagree | Mildly disagree | Agree and disagree equally | Mildly agree | Strongly agree |
| There’s nothing worse than feeling distressed or upset. | | | | |
| Strongly disagree | Mildly disagree | Agree and disagree equally | Mildly agree | Strongly agree |
| I can tolerate being distressed or upset as well as most people. | | | | |
| Strongly disagree | Mildly disagree | Agree and disagree equally | Mildly agree | Strongly agree |
| My feelings of distress or being upset are not acceptable. | | | | |
| Strongly disagree | Mildly disagree | Agree and disagree equally | Mildly agree | Strongly agree |
| I’ll do anything to avoid feeling distressed or upset. | | | | |
| Strongly disagree | Mildly disagree | Agree and disagree equally | Mildly agree | Strongly agree |
| Other people seem to be able to tolerate feeling distressed or upset better than I can. | | | | |
| Strongly disagree | Mildly disagree | Agree and disagree equally | Mildly agree | Strongly agree |
| Being distressed or upset is always a major ordeal for me | | | | |
| Strongly disagree | Mildly disagree | Agree and disagree equally | Mildly agree | Strongly agree |
| I am ashamed of myself when I feel distressed or upset | | | | |
| Strongly disagree | Mildly disagree | Agree and disagree equally | Mildly agree | Strongly agree |
| My feelings of distress or being upset scare me. | | | | |
| Strongly disagree | Mildly disagree | Agree and disagree equally | Mildly agree | Strongly agree |
| I’ll do anything to stop feeling distressed or upset | | | | |
| Strongly disagree | Mildly disagree | Agree and disagree equally | Mildly agree | Strongly agree |

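### As printed, the Distress Tolerance Scale scoring runs opposite to its stated meaning; the GHSQ *Not applicable* code and one SIDAS item 2 case also need a scoring rule

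*Protocol*

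**What the plan says.** **DTS.** Protocol section 6.3 says the scale "is a 15-item self-report measure designed to assess respondents’ perceived capacity to experience and endure negative emotional states". It codes agreement from 1 (strongly disagree) to 5 (strongly agree) and gives the direction: "Higher mean scores indicate a greater tendency to withstand emotional distress". It names no reverse-scored item. Appendix C prints the 15 items, starting with "Feeling distressed or upset is unbearable to me". Section 7 lists change in the DTS among the potential mechanisms of symptom reduction.

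**Aim 1.3.** The tertiary aim asks whether the app "significantly reduces insomnia, rumination, suicide cognitions, distress tolerance, and help-seeking intentions and behaviours".

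**GHSQ.** Section 6.3 codes *Not applicable* as 0, *Extremely unlikely* as 1 and *Extremely likely* as 5, and adds: "Higher scores represent stronger intentions to seek help". Both section 6.3 and Appendix C list an item on seeking help from no one alongside the sources of help, with no reversal or separate handling.

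**SIDAS.** Section 6.1 says "Item two (controllability) is reverse scored" and gives a total from 0 to 50. In Appendix C, item 1 (frequency) accepts 0, *Never*. Item 2 then asks "In the past month, how much control have you had over these thoughts", with 0 meaning no control. No rule is printed for a respondent who has just answered *Never*.

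**The concern.** Whether a high DTS score is good or bad depends on how the items are worded, and the printed coding and the printed items disagree. Elsewhere the protocol says when items are reversed: for SIDAS item 2 (section 6.1) and for half of the Grit items (section 6.4). Silence on the DTS is therefore not obviously shorthand. If the rule is followed literally, a gain in tolerance appears as a fall in the mean, and section 6.3 would have it read as a loss.

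Aim 1.3 makes this harder to catch. It lists distress tolerance among the things the app should reduce, so a falling mean counts as success under the aim and as deterioration under section 6.3.

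For the GHSQ, the printed code ranks a person with no partner below a person who has one and would almost never turn to them. Circumstance is mixed with intention.

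For the SIDAS, the primary outcome, a respondent with no thoughts in the past month is asked how well they controlled them. The reversed answer then enters the severity score.

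**Working it through.** **DTS**

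Inputs: 15 items and codes 1 to 5 (section 6.3); item wording (Appendix C). Reading the items in order, only the sixth, on tolerating distress as well as most people do, runs in the stated direction. The other 14 express intolerance.

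- Most tolerant respondent as printed: (14 × 1 + 1 × 5) / 15 = 19/15 = 1.27.
- Least tolerant respondent as printed: (14 × 5 + 1 × 1) / 15 = 71/15 = 4.73.
- If every answer moves one category towards tolerance, the printed mean changes by (−14 + 1) / 15 = −13/15 = −0.87.
- With the 14 items recoded as 6 − x, the most tolerant respondent scores 75/15 = 5.00, the least tolerant 15/15 = 1.00, and the same one-category improvement gives +1.00.

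The printed rule thus reverses the sign. It also shrinks the change to 13/15 of its size, because the one positive item pulls the other way.

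**GHSQ**

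Inputs: the codes and the ten named sources, 3 professional + 4 informal + 3 telephone or online (section 6.3). The protocol does not say whether they are summed, averaged or analysed singly, so the sums and means below are illustrations.

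- All ten *Extremely unlikely*: 10 × 1 = 10. One *Not applicable* and nine *Extremely unlikely*: 0 + 9 = 9.
- All ten *Likely*: 10 × 4 = 40, mean 4.0. One *Not applicable* and nine *Likely*: 36, mean 3.6.
- The last respondent with *Not applicable* set to missing: 36/9 = 4.0.

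If items are analysed singly, a 0 still sits below a 1 on a scale where higher means stronger intention. The no-one item matters only if it is combined with the sources. Unreversed, it would add 5 points for being extremely likely to seek no help.

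**SIDAS**

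Inputs: five items scored 0 to 10, with item 2 reversed (section 6.1). Total = i1 + (10 − i2) + i3 + i4 + i5.

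- The stated range reproduces. Minimum: 0 + (10 − 10) + 0 + 0 + 0 = 0. Maximum: 10 + (10 − 0) + 10 + 10 + 10 = 50.
- With item 1 = 0 and items 3 to 5 = 0, the total is 10, 5 or 0 when item 2 is answered 0, 5 or 10.

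Up to 10 points, or 10/50 = 20% of the scale, can therefore come from a question about thoughts the respondent did not have. *Never* is possible even at baseline, because screening in Appendix B asks about the past 12 months while the SIDAS asks about the past month.

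**The case against.** The strongest reply on the DTS is that section 6.3 cites the published scale and gives the final direction, which can be reached only by reversing the intolerance items. On that view one sentence was left out, and item-level scoring belongs in the SAP, which is not at hand. This stands in part: a careful analyst may well recover the intended scoring, so it cannot be said that the result will be reported with the wrong sign. But the protocol prints a coding and a direction that cannot both hold, it states reversal for two other scales, and Aim 1.3 points the other way. An SAP would have to correct this text, not merely add to it.

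Aim 1.3 can fairly be called a slip in a list governed by one verb. No hypothesis in section 1.4 depends on it, and the DTS appears in none of them.

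For the GHSQ, it is true that no total is defined and that a SAP could set *Not applicable* to missing. That limits the claim to the printed code and its stated direction.

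The SIDAS part is the most exposed. Reversing item 2 is right. The survey build or the SAP may already deal with *Never*, and a respondent who answers full control scores 0 anyway. A reader might infer that the artefact dilutes the treatment effect by a definite share. The documents do not support that: it would need the proportion reporting no thoughts in each arm, how they answer item 2, and the SIDAS standard deviation, and none is given. A reader might also conclude that items 2 to 5 should be skipped after *Never*. That would suppress item 3, whose top anchor is a suicide attempt and which counts towards the above-20 threshold in sections 10.1 and 12.1 and in Appendix E.

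**Conclusion.** The DTS rule is wrong as written: applied literally, it places the most tolerant respondent at 1.27 and the least tolerant at 4.73, against a stated direction that says the reverse. This needs no assumption beyond reading the items. The consequence, a wrong sign on a named mechanism, follows only if analysts apply the printed rule.

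The GHSQ code for *Not applicable* is also wrong as printed, whether items are combined or analysed singly. The size of the effect on any summary depends on a summary the protocol does not define.

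The SIDAS point is secondary: a possible artefact of 0 to 10 points per affected respondent, of unknown frequency, and possibly already handled in material not seen.

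The DTS and GHSQ are tertiary measures and the sample size does not depend on any of this. The corrections are worth making because they are simple and remove real ambiguity. They are not grounds for doubting the primary comparison.

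**What to change.** - **DTS, section 6.3:** state that the 14 intolerance-worded items are reverse-scored (6 − x) before averaging, and that the one positively worded item is left as it is.
- **Aim 1.3:** reword so that the app reduces insomnia, rumination and suicide cognitions, and increases distress tolerance and help-seeking intentions and behaviours.
- **GHSQ, section 6.3:** treat *Not applicable* as missing, not as 0, and do not combine the no-one item unreversed with the sources of help.
- **SIDAS, section 6.1:** state that item 2 contributes 0 to the outcome score when item 1 is 0. Keep asking and scoring items 3 to 5, and keep the recorded item 2 answer. Because this lowers the total by up to 10 points in that group, the protocol should also say which total its safety checks use; that choice is for those responsible for safety.

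The cost is a few sentences and a few lines of scoring code. Participants answer the same questions. All four changes can be applied to stored item responses, so they remain possible after data collection, but they should be fixed before unblinding.
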